### To analyze non-parametric QEHD data the Wilcoxon test will be used.

**7 - GOALS**

### The present project aims to be developed within the timeframe set forth in the schedule and to start after approval by the bioethics committee. The bibliographic review will be done from September 2017 until December 2018, the work will be submitted to the bioethics committee and inserted in an international clinical records site between August and September 2017, followed by the screening period from October until November 2017. Upon completion of the screening, the randomized clinical trial will be conducted from November 2017 through September 2018. After data collection is completed, statistical analysis of the results will be done from October 2018 through November 2018. The final report will be built and submitted by December 2018 and later the scientific paper will be written for publication.

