**RESEARCH PROJECT**

**5 – AIM**

The aim of this study was to evaluate the effect of the fluorinated amorphous calcium phosphate casein-phosphorus (CPP-ACPF) associated with low-power laser therapy (TLBP) on the symptomatology and impact of the quality of life of patients with dentin hypersensitivity ( HD) by means of a randomized, parallel, placebo-controlled clinical trial. The null hypothesis tested in the present study will be:

H0 - there will be no difference in the manifestation of dentin hypersensitivity between the groups treated with TLBP, CPP-ACPF or placebo, associated or not, during one month of evaluation, and will not influence the participants' quality of life.

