**Flowchart 01. Recruitment and allocation scheme performed in the pilot study**

**6.4. Study design**

After randomization of the sample, the teeth (at least 20 for each group) will be allocated to one of the four assessment groups according to the scheme below:
[figure not shown]

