### **6.8.3. Dentin Hypersensitivity Experience Questionnaire (QEHD).**

### Participants will be given a questionnaire prior to the start of treatment, and after one month thereafter, to assess the impact of desensitizing treatment on their quality of life. The questionnaire is based on the model described by Boiko et. Al. (45) according to the Portuguese adaptation of Douglas-De-Oliveira et. Al. (46). Also, dietary habits, systemic diseases and parafunctional habits of the participants will be recorded through a questionnaire, in order to analyze through a regression analysis the possible interaction of these factors with the HD reported throughout the study.

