## **6.9. Statistical analysis**

### The values ​​corresponding to the sensitivity reported by the participants were tabulated in an Excel spreadsheet (Microsoft Windows, 2010) and analyzed with the IBM SPSS Statistics for Windows 22.0 program (IBM Corp., New York, United States). Considering the parametric data of this study, if it has normal distribution of the same to the intergroup analysis will be done with mixed ANOVA, and the specific intergroup comparison will be done with the Tukey post-hoc test. If the data are abnormal distribution the intragroup comparison will be performed from the Friedman test and the intergroup by the Wilcoxon test. A significance level of 5% will be set for all analyzes to be performed.

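### Quality of life (QEHD), part of the aim and of H0, is analysed only by an unspecified Wilcoxon test, and neither reading of it properly tests the four-arm hypothesis

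*Protocol*

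**What the plan says.** Section 5 (Aim) sets out to evaluate the treatments' effect on symptoms and on quality of life "by means of a randomized, parallel, placebo-controlled clinical trial". H0 in the same section denies a difference between the treated and placebo groups "during one month of evaluation, and will not influence the participants' quality of life".

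Section 6.4 says the sample "will be allocated to one of the four assessment groups": placebo, CPP-ACPF, laser, and laser plus CPP-ACPF.

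On collection, section 6.8.3 says: "Participants will be given a questionnaire prior to the start of treatment, and after one month thereafter". QEHD is therefore measured twice, once at baseline and once at one month.

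On analysis, the last sentence of 6.9, just above the Goals section, is all there is: "To analyze non-parametric QEHD data the Wilcoxon test will be used". It does not say paired or unpaired, within or between groups, or which score is analysed.

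The only other use of the name is in the preceding paragraph of 6.9, for sensitivity scores that are not normally distributed: "the intragroup comparison will be performed from the Friedman test and the intergroup by the Wilcoxon test". That paragraph ends: "A significance level of 5% will be set for all analyzes to be performed". Tukey is named there only as the follow-up to the mixed ANOVA of sensitivity.

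**The concern.** The hypothesis concerns four randomised arms, one of them placebo. A Wilcoxon test is either a paired test of change within one arm or a comparison of two independent groups. Neither is a four-arm test, and the protocol does not say which is meant.

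The choice matters because some improvement in every arm is to be expected. Participants enter with a VAS response of at least 4. All receive prophylaxis, a hygiene kit and brushing guidance, a gel, and real or simulated laser. A test of change within an arm cannot separate that shared improvement from a treatment effect. Finding significance in an active arm but not in placebo does not test the difference between them either. A series of two-group tests does use the placebo arm, but at 5% each it inflates the chance of some false claim. At stake is whether a statement about quality of life, one of the two outcomes in the aim, has a valid test behind it.

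**Working it through.** **Inputs from the protocol**
- Four arms (6.4, Table 2) and two QEHD time points (6.8.3).
- 5% for every analysis (6.9). Sidedness is not stated; two-sided is assumed.
- Participants per arm: about 10 blocks of four, one participant per arm per block (6.5), so 10 × 4 = 40 participants, or 10 per arm. With the 20% loss in 6.3, 10 × 0.8 = 8 per arm.
- QEHD is scored per participant, so allocation by participant as in 6.5 is assumed, although 6.4 words allocation by tooth.

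**Assumed.** The protocol gives no QEHD mean, SD or expected change. Change scores are taken as normal with SD 1. The same mean improvement of 0.5, 0.8 or 1.0 SD is given to all four arms, so there is no treatment effect.

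**The plan's own figure.** The 20 teeth per group in 6.3 rests on VAS and comes without an SD, so it can be neither confirmed nor refuted. There is no QEHD figure to reproduce, and the point does not depend on 6.3 beyond the loss rate.

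**Reading A: signed-rank test within each arm.** Simulation, 2,000 trials per row:

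| n per arm | shared improvement (SD) | a given active arm significant | at least one of three active arms |
| --- | --- | --- | --- |
| 10 | 0.5 | 29.8% | 63.1% |
| 10 | 0.8 | 61.5% | 93.8% |
| 10 | 1.0 | 79.9% | 98.8% |
| 8 | 0.5 | 20.6% | 48.9% |
| 8 | 0.8 | 41.5% | 80.8% |
| 8 | 1.0 | 60.6% | 93.6% |

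The arms are independent, so the last column can be checked as 1 − (1 − p)³. For n = 8 and 0.5 SD, 1 − 0.794³ = 0.499, against 0.489 simulated. For n = 10 and 0.8 SD, 1 − 0.3855³ = 0.943, against 0.938.

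The simulation error near 63% is √(0.63 × 0.37 / 2000) = 0.011. A repeat gave 62% / 94% / 99% at n = 10 and 48% / 82% / 94% at n = 8, which agrees within that error.

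**Reading B: rank-sum test between groups, applied to change.**
- One pair under the same conditions is significant in about 4-6% of trials, whatever the shared improvement.
- Four arms give 4 × 3 / 2 = 6 pairs. If the tests were independent, the chance of at least one false positive would be 1 − 0.95⁶ = 26.5%.
- The pairs share arms, so the simulated figure is lower: 18-22% in this run and 17-22% in the repeat.
- If only the three comparisons with placebo were made, the independent figure is 1 − 0.95³ = 14.3%.

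**A direct four-arm test.** Kruskal-Wallis on change gives about 4-5% false positives at every shared improvement and at both sample sizes.

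**The case against.** A reader might infer that the protocol plans a before/after test for QEHD and no comparison between arms. The text does not support that. The QEHD sentence contains neither idea, and the paragraph before it gives Friedman to the within-group comparison and Wilcoxon to the between-group one. If the name carries the same meaning in both places, the placebo control is kept and the Reading A percentages do not apply. This objection stands. Two time points make the paired reading plausible but do not establish it, so confidence in it is only moderate.

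A reader might also infer that the trial will declare a quality-of-life benefit when none exists. The protocol states no rule by which one significant arm counts as success, and entry is selected on VAS, not on QEHD. The percentages are chances of a significant result under an assumed shared improvement, not predictions for this trial.

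It can further be said that QEHD did not drive the sample size, that sensitivity does have a between-group analysis, and that a SAP not shown may settle the detail. The first two are true and limit the importance of the point. The third carries less weight: the protocol does not leave the method open. It names a test, and that test, taken alone, does not fit a four-arm hypothesis on either reading.

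**Conclusion.** The point holds in this form: the QEHD analysis is ambiguous, and neither meaning of the named test properly tests the four-arm H0.
- **Paired reading:** placebo plays no part. With no treatment effect, at least one active arm is significant in roughly half to nearly all trials: about 62-99% at 10 per arm and 48-94% at 8 per arm, for shared improvements of 0.5 to 1.0 SD.
- **Between-group reading:** placebo control is kept, but there is no overall test, and the chance of at least one false positive over six unadjusted pairs is about 17-22%.

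The Reading A figures depend on the assumed improvement sizes. The Reading B figures hardly do, but they suppose that all six pairs are tested. That a single Wilcoxon test does not answer a four-arm question depends on neither assumption.

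**What to change.** Replace the QEHD sentence in 6.9 with a direct comparison of arms, one record per participant:
- ANCOVA of the one-month QEHD score on arm, with baseline QEHD as covariate. The overall arm effect tests H0. Report each active arm minus placebo with its 95% CI, and apply Holm's adjustment if these three contrasts are to support separate claims.
- If the scores are clearly skewed, rank ANCOVA, or Kruskal-Wallis on change followed by Holm-adjusted pairs.
- If a Wilcoxon test is kept, say which one. Any within-arm Wilcoxon test is descriptive only.

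ANCOVA is a sound choice but not the only valid one. What is needed is a named between-arm test that controls error over the four arms.

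The cost is two or three sentences and slightly more analysis; both questionnaires are already planned. The real price is a stricter threshold for pairwise claims: Holm's first step is 0.05 / 6 = 0.0083 for six pairs, or 0.05 / 3 = 0.0167 for three comparisons with placebo. With 8 to 10 participants per arm, fewer pairwise differences will reach it.

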**7 – SCHEDULE OF ACTIVITIES**

| **ACTIVITIES** | **2017** | | | | | | **2018** | | | | | | | | | | | | **2019** |
| --- | --- | --- | --- | --- | --- | --- | --- | --- | --- | --- | --- | --- | --- | --- | --- | --- | --- | --- | --- |
|  | **Jul** | **Ag** | **Set** | **Ot** | **Nov** | **Dez** | **Jan** | **Fev** | **Marc** | **Abri** | **Maio** | **Jun** | **Jul** | **Ag** | **Set** | **Out** | **Nov** | **Dez** | **Jan** |
| Approval on ethics committee and registration on clinical research site |  |  | x | x |  |  |  |  |  |  |  |  |  |  |  |  |  |  |  |
| Literature review |  |  | x | X | x | x | x |  | x | x | x | x | x | x | x | x | x | x |  |
| Qualification exam |  |  |  |  |  |  |  | x |  |  |  |  |  |  |  |  |  |  |  |
| Development of the randomized clinical trial |  |  |  |  | x | x | x |  | x | x | x | x | x | x | x |  |  |  |  |
| Tabulation and statistical analysis of results |  |  |  |  |  |  |  |  |  |  |  |  |  |  |  | x | x |  |  |
| Elaboration and delivery of the final report. |  |  |  |  | x | x | x |  | x | x | x | x | x | x | x | x | x | x |  |
